### Inclusion criteria

The study’s inclusion criteria will include: (1) patients who have been newly diagnosed with head and neck cancer (within the previous month), whose diagnosis has been confirmed by a histopathological examination report, who have been treated only with surgery or have yet to received treatment, and who are at any cancer stage except metastasis to the central nervous system; (2) patients aged 18 years and older; (3) patients who have undergone surgery and plan to receive the standard regime of radiotherapy or chemotherapy; (4) patients who have developed depression and anxiety symptoms after their head and neck cancer diagnosis with a “Hospital Anxiety and Depression Scale” (HADS) depression subscale score of ≥ 8 and an anxiety subscale score of ≥ 8; and (5) patients who are able to read and understand written Malay.

### Exclusion criteria

Patients will be excluded if they: (1) have a history of pre-existing psychiatric illness; (2) have a history of illicit drug use, substance use disorder, alcohol use disorder, substance-related disorder, or alcohol-related disorder (patients will be screened via urine dipstick for drugs and the “Mini International Neuropsychiatric Interview” to exclude these conditions); (3) have a history of medical illness that can induce psychiatric symptoms; (4) currently receive any psychotherapy or counseling; (5) are physically unfit for this study’s interventions (for example those who are bed-bound or too weak to engage in the study interventions); (6) exhibit cognitive impairment (patients will be screened via the “Mini Mental State Examination” and patients who receive a score of < 24/30 will be excluded); (7) have received any pharmacotherapy for anxiety and depression symptoms developed after their cancer diagnosis; and (8) are pregnant.

### Recruitment process

This study will use a consecutive sampling method. The research team will approach head and neck cancer patients registered at the two targeted institutions and explain the study’s objectives and procedures. Patients who are interested in participating in this study will be screened for inclusion and exclusion criteria by a research team member. All eligible patients will be invited to participate in this study. The study’s purposes and procedures will be thoroughly explained (verbal explanation by the research assistant and a copy of the participant information will also be distributed) to prospective participants before they are invited to participate in this study, their anonymity will be assured, and they will be informed of their right to withdraw from the study at any time and the data collected will be discarded. Eligible patients will be given 48 hours to decide on their participation in the study. Then, participants will sign written informed consent to participate in the study before they enroll in the study.

### Randomization

This study will use stratified permuted block randomization, stratifying trial participants according to their age (*18 to 40 years old*, *41 to 60 years old*, and *over 60 years old*) and gender (*male* and *female*). Participants will be randomized into three groups: an ACT group, an MBSR group, and a control group of patients on treatment-as-usual for intervention. Using a 1:1:1 allocation ratio and block randomization, we will randomly assign participants to the three groups. An allocation sequence will be generated via computer-generated random numbers, which will be obtained by a research assistant who is not otherwise involved in this study. The allocation sequence will be concealed in an opaque, sequentially numbered envelope.

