## Methods/Design

### Design

The current study will conduct a multicentre, three-armed, parallel-group, double-blind RCT that is expected to run for three years.

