### Setting

This study will be conducted in Advanced Medical and Dental Institute (AMDI) at the Universiti Sains Malaysia (USM) and Universiti Kebangsaan Malaysia Medical Centre (UKMMC). AMDI, USM is a tertiary referral center for oncology in Peninsular Malaysia while UKMMC is a tertiary referral center for various illnesses, including oncology cases in Peninsular Malaysia.

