### Interventions

An eight-week psychosocial intervention will be administered to participants in each intervention group (MBSR and ACT) while participants in the control group will receive treatment-as-usual. The study’s outcomes will be assessed at three times: pre-intervention (t_0_), immediately after the eight-week intervention (t_1_), and 24 weeks after the intervention (t_2_).

Both the ACT and MBSR interventions will comprise eight sessions delivered at a rate of one session per week. Each session will last for one hour. At AMDI, USM, and UKMMC, chemotherapy for head and neck cancer lasts for 8 weeks, delivered at a rate of one session per week. Similarly, radiotherapy for head and neck cancer lasts for eight weeks at these institutions. Therefore, this study’s ACT and MBSR sessions will align with participants’ chemotherapy or radiotherapy sessions to ensure that all participants attend their intervention sessions. ACT and MBSR will be provided in group settings with intervention groups of 10 participants each.

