### Data analysis

All of this study’s data analysis will be conducted using the Statistical Package for Social Sciences, version 26 (SPSS 26; SPSS Inc., Chicago, Illinois, USA). Initially, the baseline sociodemographic and tumor characteristics will be presented by randomized groups (ACT, MBSR, and control groups).

The mean difference in the primary outcome (total PTGI-SF score) for the three randomized groups (ACT, MBSR, and control groups) at each specific time point (pre-intervention [t_0_], post-treatment at 8 weeks [t_1_] and 24 weeks after intervention [t_2_]) will be assessed using one way analysis of variance (ANOVA) followed by false discovery rate adjustment. For the main pool analysis, mixed linear model will be employed for comparing the primary outcome (total PTGI-SF score) between ACT and control groups and between MBSR and control groups across the three time points (t_0_, t_1_ and t_2_), while controlling for stratification factors such as age and gender. The main effects of intervention in the groups and time points will be presented as estimated marginal mean and standard error of mean. The study’s primary analysis will follow the intention-to-treat (ITT) principle. The data analysis for the study’s secondary outcomes (quality of life, hope, optimism, depression, anxiety, and EA) will be conducted similarly to the primary outcomes’ calculation. In addition, 95% confidence interval will also be presented alongside the main effect. Statistical significance will be two-tailed and set to *p* < 0.05.

To handle any missing data, if the missing data represent less than 5% of the study’s total collected data, they will be ignored. If the missing data represent more than 5% but less than 40% of the total collected and are assumed to be randomly missing, then multiple imputation (restricted maximum likelihood estimation) will be performed using Stata 15. However, if the missing data represent more than 40% of the total collected data or are assumed to be missing either not randomly or completely randomly, then only the collected data will be used for the study’s analysis, and the missing data will be explained as a research limitation in any publications of the study’s findings [68].

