Since this study will only utilize a maximum of four therapists to conduct the intervention sessions, this may limit the generalizability of the study findings. Hence, it is of utmost importance to train up more therapists for future randomized clinical trials which investigate efficacy of ACT and to deliver this intervention to cancer patients in oncology settings. The first step in training for therapists is to set up ACT workshop which will allow ACT trainee to experience the metaphors and exercises used in ACT on a personal context and as a receiver of ACT. This step of organizing ACT workshop for trainee therapists serve several benefits and advantages. Participants in ACT workshop exhibited not only increase in knowledge regarding ACT, but also develop interest for further learning and utilize ACT concepts and utilize ACT practices in their clinical work [70]. Moreover, trainee therapists should be encouraged to join their supervisors in regular individual or group ACT sessions in addition to their regular supervision hours. During supervision hours, trainee therapists are encouraged to conceptualize a case based on the ACT perspective and report on the progress of the case on a weekly basis. The core learning objectives for the trainee therapists should be based on three principles: (1) to develop a sense of personal wholeness and able to reflect the same sense to the patients who experience EA, (2) to be able to help patients to accept emotions and thoughts by reflecting their own experience to the experience of the patients, and (3) to be able to guide patients to understand the costs of EA on their personal values in life, so that patients are willing to commit substantially towards actions to pursue their values in life.

In addition, since this study only recruit Malaysia head and neck cancer patients, future RCT with larger sample size (under medium to large effect size) and patients recruited from multiple countries is warranted to evaluate the effects of ACT and MBSR on positive psychology (such as PTG, hope optimism), quality of life and negative outcomes (such as depression, anxiety and EA).

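### Hospital is in neither the stratification nor the main model of this two-hospital trial, so chance hospital imbalance between arms stays unadjusted: a small loss, removed by one model term

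*Protocol article*

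**What the plan says.** The Design section of the protocol article states: "The current study will conduct a multicentre, three-armed, parallel-group, double-blind RCT". Setting names the two sites. It describes one as a tertiary oncology referral centre and the other as a tertiary centre for various illnesses, oncology included. Participants draws patients from the oncology and otorhinolaryngology units of each.

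On allocation, Randomization reads "This study will use stratified permuted block randomization, stratifying trial participants according to their age", followed by three age bands and by gender. That makes 3 × 2 = 6 strata. The section continues: "Using a 1:1:1 allocation ratio and block randomization, we will randomly assign participants to the three groups". Hospital is not listed.

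On analysis, Data analysis specifies a mixed linear model comparing ACT with control and MBSR with control over the three assessments, "while controlling for stratification factors such as age and gender". The words 'such as' leave the list formally open, but Randomization gives no third stratification factor. As written, hospital does not enter. The secondary outcomes are to be analysed in the same way.

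**The concern.** Each hospital has its own clinics, and Interventions aligns the sessions with the participant's chemotherapy or radiotherapy, so a patient's care is organised around one site. If outcomes differ between the hospitals, an arm that happens to hold more patients from one of them carries part of that difference into the treatment contrast. Stratification would limit such an imbalance, and a covariate would correct for it. The plan does the one for age and gender, and the other for the same two factors, but does neither for hospital. At stake is an avoidable chance shift in any one trial's estimate, plus a little precision. The document gives no figures on how far the hospitals differ, so the size has to be explored under assumptions.

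**Working it through.** The plan states no figure on hospital balance, so there is none to reproduce. The claim does not depend on the sample size calculation beyond the planned numbers.

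**Inputs from the protocol article.** 120 patients, 40 per arm (Participants); 1:1:1 permuted blocks within 6 age-by-gender strata (Randomization); two hospitals (Setting).

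**Assumed inputs.** Block size 6; stratum shares 0.08, 0.07, 0.30, 0.15, 0.28 and 0.12; hospital splits of 50:50, 70:30 and 80:20; hospital effect on the outcome of 0.3 to 0.5 SD.

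**Step 1: how often imbalance arises.** The stated scheme was simulated with hospital ignored, 8,000 trials per split. The measure is the absolute ACT–control difference in the share of patients from one hospital.

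| Hospital split | Mean gap (points) | Gap ≥ 10 points | Gap ≥ 20 points |
|---|---|---|---|
| 50:50 | 9.1 | 38% | 8% |
| 70:30 | 8.1 | 33% | 5% |
| 80:20 | 7.1 | 25% | 2% |

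A hand check agrees. The SD of the difference is √(2p(1−p)/40). At p = 0.5 this is √(0.5/40) = 0.112. A 10-point gap is then 0.10/0.112 = 0.89 SD (two-sided normal probability 37%), and a 20-point gap is 1.79 SD (7%).

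**Step 2: what a gap does to the contrast.** Shift = gap × hospital effect. For a 20-point gap, 0.20 × 0.3 = 0.06 SD and 0.20 × 0.5 = 0.10 SD. The standard error of a 40-versus-40 difference at one time point is √(2/40) = 0.22 SD. The shift is thus about 0.27 to 0.45 of a standard error. For a 10-point gap it is half that: 0.03 to 0.05 SD.

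**Step 3: precision.** The ratio of the standard error without hospital to that with it is about √(1 + d²p(1−p)). At p = 0.5:
- d = 0.3: √(1 + 0.09 × 0.25) = 1.011
- d = 0.5: √(1 + 0.25 × 0.25) = 1.031

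The loss is therefore about 1% to 3%.

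**Step 4: validity.** A 40-versus-40 linear model was simulated under no treatment effect, 50:50 split, 8,000 trials. The rejection rate without and with hospital was 4.6% and 4.5% at 0.3 SD, and 5.0% and 5.0% at 0.5 SD. Both sit near the nominal 5%.

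**The case against.** The strongest reply is that nothing is invalid. Allocation is random, so the contrast is unbiased on average, and chance imbalance is already part of the standard error. Step 4 bears this out, and the point stands in full. A reader might infer that omitting hospital biases the trial; the documents and the calculation do not support that.

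Second, the hospital difference is assumed. Both sites are tertiary centres treating cancer, with one set of eligibility criteria and the same stated durations of chemotherapy and radiotherapy. That also stands, so the 0.3–0.5 SD range is illustrative. Further, where the contrast is change from baseline, a constant hospital difference cancels and only a difference in change matters. The one-way ANOVAs at each time point lack that protection.

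Third, a separate analysis plan is mentioned under Blinding and could name hospital. It could, but the article already states which factors the model controls for, and hospital is not among them.

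Three stronger readings are tempting and do not hold:
- **Therapists.** The Discussion says "this study will only utilize a maximum of four therapists to conduct the intervention sessions", and a reader might infer that hospital imbalance becomes therapist imbalance. Treatment fidelity gives ACT and MBSR each a primary and a backup therapist, so therapists are tied to arm. A hospital term could not remove their differences.
- **Envelopes.** From "The allocation sequence will be concealed in an opaque, sequentially numbered envelope" one might infer that a series shared by two sites must be split and its blocks broken. The article does not say where envelopes are held, and Blinding has one research assistant make the assignments, which is compatible with central allocation.
- **Group size.** From "ACT and MBSR will be provided in group settings with intervention groups of 10 participants each" one might infer that uneven hospital numbers leave groups unfilled. The article does not say that groups run within hospitals. Stratifying would not secure full groups either: at a 70:30 split a perfectly stratified arm of 40 has 28 and 12 patients.

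**Conclusion.** The point holds as a modest one. Hospital is absent from both the stratification and the stated model, so chance imbalance between arms is neither limited nor corrected. Gaps of 10 points or more between ACT and control are common (about 25–38% of trials) and gaps of 20 points or more are uncommon (about 2–8%). A 20-point gap moves the contrast by 0.06–0.10 SD against a standard error of about 0.22 SD, and omission costs about 1–3% of the standard error. The frequencies rest on the assumed block size, stratum shares and hospital splits; the shifts and precision loss rest on the assumed hospital effect and a comparison at a single time point. There is no bias on average and no inflation of type I error. The case for change is that the remedy costs almost nothing.

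**What to change.** In Data analysis, name hospital as a fixed effect next to age and gender in the mixed model, for the primary and all secondary outcomes, and fix this before unblinding. The cost is one degree of freedom. If the reported contrast is change from baseline, state also whether hospital is crossed with time: a main effect adjusts for level only, and the interaction over three assessments takes two further degrees of freedom.

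If recruitment has not started, separate blocked lists per hospital are an option. That doubles the strata from 6 to 12, averaging 120/12 = 10 patients each, so more blocks stay incomplete and arm sizes may drift by a few patients. At this sample size, keeping age and gender alone in the allocation is defensible provided hospital is in the model.

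Therapist and therapy-group effects should be dealt with as a separate matter; the hospital term does not address them.

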### Interventions

An eight-week psychosocial intervention will be administered to participants in each intervention group (MBSR and ACT) while participants in the control group will receive treatment-as-usual. The study’s outcomes will be assessed at three times: pre-intervention (t_0_), immediately after the eight-week intervention (t_1_), and 24 weeks after the intervention (t_2_).

Both the ACT and MBSR interventions will comprise eight sessions delivered at a rate of one session per week. Each session will last for one hour. At AMDI, USM, and UKMMC, chemotherapy for head and neck cancer lasts for 8 weeks, delivered at a rate of one session per week. Similarly, radiotherapy for head and neck cancer lasts for eight weeks at these institutions. Therefore, this study’s ACT and MBSR sessions will align with participants’ chemotherapy or radiotherapy sessions to ensure that all participants attend their intervention sessions. ACT and MBSR will be provided in group settings with intervention groups of 10 participants each.

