### Participants

This study’s participants will be recruited from the source population. This population includes all newly diagnosed head and neck cancer patients who have been treated only with surgery or who have not yet received treatment and who are registered under the oncology and otorhinolaryngology unit of the Advanced Medical and Dental Institute (AMDI) at the Universiti Sains Malaysia (USM) or the oncology and otorhinolaryngology unit of Universiti Kebangsaan Malaysia Medical Centre (UKMMC). The study’s sample size was determined based on G-Power 3.1.9.2 for analysis of variance (ANOVA). This sample size was calculated based on continuous responses to the posttraumatic growth inventory used in the study by Labelle et al. (2015) [48] with a medium effect size (0.15) and a two-tailed alpha of 0.05. The results of this calculation indicated that the current study requires a total sample of 93 for three equal-sized groups to achieve a power of 0.8. Anticipating a drop-out rate of 30%, we estimated a total sample size of 120 respondents and 40 respondents for each group.

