### Treatment fidelity

ACT will be conducted for the ACT intervention group by a therapist trained in ACT, who will have a trained backup therapist on standby to replace the primary therapist when necessary. Similarly, MBSR will be conducted for the MBSR group by a therapist trained in MBSR, and a trained backup therapist will be on standby to replace the primary therapist when necessary. All the study’s therapists and backup therapists will be postgraduate students in psychology who are not otherwise involved in the study. All the therapists have two-year experience of conducting psychotherapy. They will also receive training manual detailing the psychotherapy sessions for both ACT and MBSR, and they will also undergo 2 full days of brief training workshop for ACT and MBSR from the principal investigator. As for monitoring of treatment integrity, a psychiatrist and a clinical psychologist, both trained in ACT and MBSR will measure the delivery of the interventions by all the therapists in the ACT and MBSR groups independently. 15% of audio-recording of the psychotherapy sessions will be randomly selected and stratified according to therapist and the phase of intervention (early, middle or end) and then, treatment integrity assessments will be performed by using: (1) the Drexel University CT/ACT Therapist Adherence and Competence Rating Scale (DUACRS) [53] for ACT sessions and (2) the Mindfulness-Based Interventions: Teaching Assessment Criteria (MBI:TAC) [54]. Each treatment integrity assessor will assess half of the selected sessions. Finally, the interrater reliability of the two treatment integrity assessors is computed to assess the treatment integrity of all the therapists in delivering the interventions [55]. In addition, the principal investigator will discuss issues regarding the delivery of the interventions with the therapist who is inconsistent in conducting the ACT and MBSR sessions.

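### The sample size makes no allowance for delivery of ACT and MBSR in groups of 10, and the stated analyses carry no therapy-group term

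*Protocol article*

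**What the plan says.** Participants are randomised individually in a 1:1:1 ratio, 40 per arm (protocol article, Participants and Randomization). Treatment is then shared: "ACT and MBSR will be provided in group settings with intervention groups of 10 participants each" (Interventions). The section on MBSR makes exchange of experience between participants part of the sessions. The control arm also has eight weekly sessions, but the Treatment-as-usual section does not say that they are held in groups.

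The sample size comes from G-Power for an ANOVA, "with a medium effect size (0.15) and a two-tailed alpha of 0.05" (Participants). It requires 93 in total for power 0.8, raised to 120 for 30% dropout. No ICC or design effect is mentioned.

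Under Data analysis, total PTGI-SF is compared across the three arms by one-way ANOVA at each time point. The main analysis is a mixed linear model of ACT against control and MBSR against control over three time points, "while controlling for stratification factors such as age and gender". No term for therapy group is described. The Discussion raises the small number of therapists, but only as a limit on generalisability.

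**The concern.** People treated together share sessions, peers, timing and a therapist, so their outcomes may be more alike than those of people treated apart. Individual randomisation does not remove this, because the grouping arises after allocation. A method that treats all 40 participants in an active arm as independent then overstates the information in that arm. Confidence intervals would be too narrow, type I error would exceed 5%, and the trial would have less power than stated. The primary outcome and all secondary outcomes are affected, since the secondary outcomes are to be analysed in the same way.

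**Working it through.** **Inputs from the protocol article.** 40 per arm and groups of 10, so 40/10 = 4 groups per active arm; effect size 0.15 (read as Cohen's f); alpha 0.05; k = 3 arms; T = 3 time points; N = 93.

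**Assumed, because not given.** Correlation between time points ρ = 0.5 and sphericity (common defaults); ICC of 0.01, 0.05 and 0.10. The ICC is taken to apply to the effect being tested, that is, to change after baseline.

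**Step 1: reproduce 93.** For the arm-by-time interaction in a repeated-measures ANOVA with independent participants:

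- λ = N f² T/(1 − ρ) = 93 × 0.0225 × 3/0.5 = 12.555
- df = (3 − 1)(3 − 1) = 4 and (93 − 3)(3 − 1) = 180; critical F = 2.42
- power = 0.811; at N = 90 it is 0.796

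So 93 is the smallest total in three equal arms that reaches 0.8, and clustering plays no part in it. A one-way ANOVA with f = 0.15 would need 432, so that is not the calculation behind 93.

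**Step 2: power with clustering.** The design effect is DE = 1 + (n − 1) × ICC, with n the group size. At N = 93 there are 31 per arm, or 31/4 = 7.75 per group. With the two active arms clustered and control not, the average design effect is approximately (1 + 2 × DE)/3, and λ is divided by it.

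| ICC | DE (n = 7.75) | Average over arms | λ | Power | Bound: all arms clustered, n = 10 (DE; power) |
|---|---|---|---|---|---|
| 0.01 | 1.0675 | 1.045 | 12.01 | 0.79 | 1.09; 0.77 |
| 0.05 | 1.3375 | 1.225 | 10.25 | 0.72 | 1.45; 0.63 |
| 0.10 | 1.675 | 1.45 | 8.66 | 0.63 | 1.90; 0.50 |

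**Step 3: actual error of a nominal 5% test that ignores the groups.** The true standard error divided by the naive one is r = √((1 + DE)/2) for active against control (one arm clustered) and r = √DE for ACT against MBSR (both clustered). The actual error is 2 × {1 − Φ(1.96/r)}.

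| ICC | Active vs control, n = 7.75 | n = 10 | ACT vs MBSR, n = 7.75 | n = 10 |
|---|---|---|---|---|
| 0.01 | 5.4% | 5.5% | 5.8% | 6.0% |
| 0.05 | 7.0% | 7.7% | 9.0% | 10.4% |
| 0.10 | 9.0% | 10.4% | 13.0% | 15.5% |

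A simulation of a plain t-test with four groups of 10 per clustered arm (40,000 runs per setting) agrees: 5.5%, 7.7% and 10.4% with one arm clustered, and 6.0%, 10.5% and 15.7% with both.

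**The case against.** **The mixed model might already handle this.** The article gives no random-effects structure, not even for participant, and the Blinding section says that a statistical analysis plan is set before final unblinding. A reader might infer that the protocol commits to treating participants as independent in the mixed model. It does not say so; it only describes the model without a group term. This part of the objection stands. It does not reach the sample size, which is fixed and has no allowance, or the one-way ANOVAs, which have no place for such a term.

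**The harm depends on an unknown.** This also stands. If the ICC is zero there is no problem, and at 0.01 the loss is about two points of power.

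**The worst figures are not the central ones.** A reader might take power of about 0.63 at ICC 0.05 as the expected result. That figure clusters the control arm, which is not said to be treated in groups, and combines the number left after dropout with full groups of 10. Likewise, error rates up to 16% belong to ACT against MBSR. That comparison is in the primary objective but is not a contrast named for the mixed model.

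**There is spare recruitment.** If all 120 were retained and only the active arms were clustered in tens, an ICC of 0.05 would be absorbed: λ = 120 × 0.0225 × 6 = 16.2, the average DE is (1 + 2 × 1.45)/3 = 1.30, and 16.2/1.30 = 12.46, close to 12.555. But the extra participants are planned to offset 30% dropout.

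**Therapist and site.** Because "this study will only utilize a maximum of four therapists to conduct the intervention sessions", a reader might count therapist effects as part of the same defect. Treatment fidelity assigns one primary therapist and a backup to each intervention, so therapist is largely confounded with arm and a therapy-group term cannot separate the two. Site is not nested in arm under individual randomisation; whether to adjust for it is a separate question.

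**Conclusion.** The point holds in a bounded form. The sample size contains no allowance for group delivery, and the analyses as described contain no therapy-group term. For any positive within-group correlation, the stated analyses give standard errors that are too small for contrasts involving ACT or MBSR, and the 0.8 power is overstated. At ICC 0.05 the working estimate is power of about 0.72 and an actual error of 7–8% for active against control. For ACT against MBSR the error is about 6%, 9–10% and 13–16% at ICC 0.01, 0.05 and 0.10. The absence of an allowance is well established. The size of the harm is conditional on the assumed ICC, on ρ = 0.5 with sphericity, and on control sessions not being run in groups. The documents do not support a claim that the loss is known to be large.

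**What to change.** - Record a therapy-group identifier for each ACT and MBSR participant prospectively, and for controls if their sessions are held in groups.
- In the primary and secondary mixed models, add a partially nested random intercept for therapy group (ACT and MBSR, and control only if grouped), with small-sample degrees of freedom. Let it act on the post-baseline assessments: an intercept held constant over all three time points would cancel out of change from baseline.
- Base inference on that model, and keep the one-way ANOVAs as descriptive.
- State that the 0.8 power assumes independence, and show the range over ICC 0.01 to 0.10.
- Acknowledge that therapist is largely confounded with arm and that this term does not repair it.

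The cost is one identifier, one model term and a short statement; treatment and recruitment are unchanged. The downside is wider intervals and a poorly estimated variance component with about four groups per active arm. The lost power is disclosed, not recovered.
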